#### The Motivational Messaging Database

The messaging database includes 500 messages that were developed in our prior RCT, consisting of both expert-written messages and peer-written messages [23]. Expert-written messages were developed through an iterative expert group review process (behaviorists, physicians, and nurses). These messages were informed by current guidelines [24] and the Social Cognitive Theory [25], which incorporates vicarious learning, verbal persuasion, and expert messages that reflect the theoretical determinants of quitting such as positive outcome expectations and self–efficacy­-enhancing small goals [25]. Peer-written messages were written by current and former smokers responding to an online survey that presented four scenarios tailored by gender, age, and readiness-to-quit. These messages were then reviewed for use in our system. More details of our methodology to generate peer written messages have been previously published [23].

#### The Standard Computer-Tailored Health Communication System

Our comparison standard CTHC is a rule-based (if-then-else) system that tailors messages based on a smoker’s readiness to quit. For example, when a smoker logs on to Decide2Quit and indicates their readiness as “not ready to quit,” a message from those categorized for “not ready to quit” smokers will be picked at random and sent to the smoker. Similarly, if the smoker indicates their readiness as “set a quit date,” a message categorized for “set a quit date” smokers will be sent to the smoker. This system was tested in our prior study and demonstrated to be effective in increasing the 6-month smoking cessation by 9% (odds ratio [OR] 1.69, 95% CI 1.03-2.8) over a nonmessaging control [26]. Thus, our comparison will be a robust, active, and effective standard CTHC system.

#### Recommender Computer-Tailored Health Communication System

The details of our development and evaluation of the recommender system were previously published [20,26,27]. Briefly, we developed a hybrid recommender system that uses three input data sources to generate the recommendations, including metadata description of the messages, implicit feedback data, and explicit feedback data (smokers in the prior and current study). The recommender system consists of multiple components.

Our metadata includes a comprehensive coding of the messages. We developed these codes to facilitate further understanding of what did and did not work in these messages. These codes include constructs from multiple behavioral theories such as the Social Cognitive Theory, the Transtheoretical Model, and the Theory of Reasoned Action [28]. We also coded the messages for content that may be pertinent to a specific user, including health and lifestyle status, health issues, and treatment options. Overall, we developed 48 codes divided into 8 categories (General Treatments, Behavioral Treatments, Over the Counter and Prescription Treatments, Motivations, Health, Sociocultural Attributes, Author Attributes, and Author Interaction). Implicit feedback data are derived from user actions. As our implicit feedback data, we used the website return data of 900 smokers that participated in our prior RCT [19]. When an email was sent to these smokers, we tracked their website usage in the days following the email. Thus, we had data on the frequency at which each message promoted the use of Decide2Quit and the characteristics of the smokers that received these messages. Explicit feedback data consist of self-reported item ratings. We recruited 846 current or former smokers from online and local sources to rate the messages on the influence scale (see Data Collection and Outcomes). Each smoker was asked to rate 20 messages, resulting in 16,920 ratings. Several classic and state-of-the art collaborative filtering methods were evaluated for accurate prediction methods. The Bayesian Probabilistic Matrix Factorization (BPMF) was identified as the best single model in our evaluation and was used to develop the recommender CTHC. The BPMF model estimates a probability distribution over a joint embedding of users and items into complementary latent spaces. The rating a given user supplies for a given item is approximated by the expected value of the product of the latent user and item factor vectors representing the user-item pair, with the expectation taken over the uncertainty in embeddings [29]. In addition to explicit feedback ratings from smokers in prior studies, the recommender CTHC is programmed to use the explicit ratings of smokers receiving the messages (see Data Collection and Outcomes).

### Access to a Peer Recruitment Toolset

The primary element of the peer recruitment toolset is our Facebook website plugin [20,26,27]. The Facebook plugin will allow smokers to browse through their Facebook friends and recruit them by sending private recruitment messages. In our pilot study [20,26,27], providing smokers access to peer recruitment quadrupled our sample (190 smokers recruited 569 more smokers to the Decide2Quit DISC). Further, the smokers recruited by their peers were more likely to be African American as compared to those who were directly recruited from an online social network (23.8% vs 10.8%; *P*<.01 for all comparisons). Thus, in our dissemination hypothesis, we are testing if providing smokers access to peer recruitment specifically increases the proportion of African Americans in our sample.

**Figure 1 figure1:**
[figure not shown]
Flow of participant randomization. Allocation to receive the peer recruitment tools occurs in two phases or waves. Wave 1: Half of the enrolled smokers are randomized to receive peer recruitment tools, while the others do not receive the tools; and Wave 2: All subsequent smokers who are randomized to the effectiveness trial and also report they were peer-recruited are given access to the peer-recruitment tools.

The basic flow of a single hypothetical smoker through the peer-referral, registration, and subsequent initiation of new peer-recruitment is described in Figure 1. Peer recruitment will take place in waves. As is common in peer recruitment approaches, to initiate the waves, we will recruit the first wave (wave 0 or seeds) of smokers. Seeds will be recruited using online advertisements. Once a seed registers on Decide2Quit and receives the peer recruitment toolset, we expect the following to occur:

The seed consents to be in the study and recruit smokers from his/her network using the peer-recruitment tools (by sending a Facebook private message).The successfully peer-recruited smoker (wave 1 recruit) registers on the system and consents to recruit other smokers in his/her social network.The wave 1 recruit then continues the peer-recruitment chain, recruiting smokers his/her their social network.The successfully peer-recruited smoker then registers (wave 2 recruit). The waves progress until the target sample size is reached.

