### Study Design

As noted in Figure 1, all participants registering online on the Decide2Quit DISC will first undergo an effectiveness randomization and then a peer recruitment allocation. The effectiveness randomization will randomly assign participants to either receive access to the recommender system CTHC or the standard CTHC. The peer recruitment allocation will depend on the recruitment source. As noted in the section below, we will either directly recruit participants to the study (via search engine advertisements and research match) or they will be recruited by their peers (peer recruited). Directly recruited peers will be randomized to either receive the peer recruitment toolset or not receive the toolset. All peer recruited participants will receive access to the peer recruitment toolset. We are using this approach for the peer recruited smokers to enhance blinding. This decision was made because these recruited smokers may communicate with their peers about the intervention.

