**1-month measures**			
	User feasibility and acceptability	User feedback on use of the system	
	Peer recruitment success	Number of peer recruiters Number of peers recruited	Reach, Adoption, Effectiveness
	Peer recruitment experience	Number of friend/family smokers a recruiter contacted for recruitment (network reached) Use of tools outside the Smoker-2-Smoker peer recruitment toolset Barriers/facilitators to peer recruitment Primary reasons a potential recruitee chose to be peer recruited or not	Reach, Implementation, Maintenance
	Perceived influence of peer recruitment on cessation	Beneficial to the participant’s quit smoking efforts Motivated to get support from those around the participant to quit smoking Increased the participant’s craving for cigarettes Made the participant feel like they were being helpful to their family and friends who are smokers	Effectiveness

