### Sample Size

#### Hypothesis 1: Dissemination

Our previous work [26,27] showed that having access to peer recruitment increased the proportion of African Americans to 23%, compared to 11% in the initial seeds (those recruited by advertisements). Using 10% as the base rate in the nonpeer recruitment group (no access to peer recruitment), we estimated sample size requirements by varying the proportion in the peer recruitment from 16% to 20%. With these assumptions, for our primary aim, we will need 219 smokers in each group to detect a difference of 10% (power=80%, α=.05). If we reduce the difference to 8% and 6%, we will need 319 and 525 participants in each group, respectively. Given that we will work with our panel to encourage recruitment of African American smokers in the peer recruitment group and may see bigger differences than those in our pilot study, we will have adequate power, particularly with the proposed sample size of 600 in each recruitment method. For recruitment time, previous trials estimated that the mean number of days to recruit a sample of 700 smokers was 244 (SD 81) days [27,40]. Assuming that peer recruitment proceeds with the same rate and SD, we can detect a difference in recruitment time as low as 14 days. Since we expect the comparison rate to be much slower, we are adequately powered to detect differences with a sample of 600 (power=80%).

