### Statistical Analyses

All primary analyses will be conducted on an intent-to-treat basis. Secondary analyses will explore dose-response effects among those with variable levels of adherence to the intervention. All analyses will be two-sided, and the alpha error will be set at .05. We will begin our analysis by examining univariate statistics (means, medians, SDs, and 95% CIs) and distributions. We will examine the balance of participant characteristics by study groups and account for any imbalances in our multivariable analysis. As appropriate, differences in measured characteristics (ie, demographics and prebaseline smoking behaviors) by group will be tested using Chi-square tests of independence (categorical variables), analysis of variance (continuous variables), or the equivalent nonparametric tests, depending on the distribution of the variables. Differences in baseline characteristics of the intervention and comparison groups will be assessed.

To test Hypothesis 1, we will categorize the smokers as either African Americans or not, and then use the chi-square statistic to test for differences between the peer recruitment and standard groups. We will also compare mean recruitment time between the two types of recruitment method using a *t* test. We will explore possible factors that may not be balanced between the smokers recruited from the two methods. If we find any significant differences, we will develop a linear regression model to further adjust for the influence of the confounders on the time to recruitment outcome. Within the peer recruitment groups, we will conduct a secondary analysis examining differences in demographic characteristic between peer recruited and directly recruited smokers. Using data provided by search engine advertisement managers, we will evaluate the performance of our online advertisements (number of users registered on Decide2Quit following an advertisement on the search engine).

To test Hypothesis 2, we will use a generalized linear model, which includes indicators of peer recruitment and recommender CTHC and the interaction between the two indicators as independent variables.

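### For H1A, every peer-recruited smoker falls in the toolset group whoever recruited them, so the contrast with the no-access group is not protected by randomisation and can show a difference when the toolset has no effect

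*Protocol article*

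**What the plan says.** Directly recruited smokers are randomised to toolset or no toolset; the Figure 1 legend says "Half of the enrolled smokers are randomized to receive peer recruitment tools, while the others do not receive the tools". Later entrants who say a peer recruited them are not randomised on this factor: "All subsequent smokers who are randomized to the effectiveness trial and also report they were peer-recruited are given access to the peer-recruitment tools". The Study Design section repeats the rule, "All peer recruited participants will receive access to the peer recruitment toolset", and justifies it by blinding, because these smokers may talk to their peers about the intervention. Neither place makes the rule depend on who did the recruiting.

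For H1A, Statistical Analyses classifies smokers as African American or not and will "use the chi-square statistic to test for differences between the peer recruitment and standard groups". The sample size section describes the comparator as "Using 10% as the base rate in the nonpeer recruitment group (no access to peer recruitment". The peer recruitment side mixes both kinds of entrant, since Statistical Analyses adds: "Within the peer recruitment groups, we will conduct a secondary analysis examining differences in demographic characteristic between peer recruited and directly recruited smokers".

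The question itself is worded in two ways. The section on access to the toolset says the hypothesis is whether giving smokers access raises the African American proportion. The hypotheses box in the Introduction sets peer recruitment against standard online recruitment.

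**The concern.** Put the access rule and the comparator together. Among directly recruited smokers, a coin decides who is in which H1A group. Among everyone else, having been peer-recruited decides it, and peer recruitment is what the toolset is meant to bring about. The no-access group can hold no peer recruits at all. If a no-toolset participant tells a friend about the open website and the friend registers and says so, the friend enters the peer recruitment group.

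What is at stake is the causal reading of H1A. In the pilot, peer recruits were more often African American than direct recruits (23.8% v 10.8%). If ordinary word of mouth has some of the same tendency, referrals from the control arm raise the proportion on the toolset side and leave the control side untouched. A toolset that adds nothing to word of mouth would then appear to work. The protections in Statistical Analyses (covariate adjustment, the recruiter marker, the complier-average analysis) are set out as steps for models of smoking cessation. None is applied to the H1A chi-square.

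**Working it through.** **The plan's own figures.** For 10% v 20%, 18% and 16% African American, 80% power and two-sided alpha of 0.05, the pooled two-proportion formula gives 199, 295 and 492 per group. With the continuity correction it gives 219, 319 and 525, exactly as stated. The sample sizes are sound for two independent groups. The issue is who belongs to the groups.

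**Inputs.** Total of 1200 (Study Overview). 10% African American among direct recruits (Sample Size, Hypothesis 1). 23.8% among peer recruits (pilot, toolset section). Two-sided alpha of 0.05 (Statistical Analyses). *Assumed, not in the protocol:* the toolset has no effect, so each randomised arm of direct recruits brings in the same number r of peers with the same racial mix q.

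**Formula.** Direct recruits per arm: s = 600 − r. By the access rule the toolset group has s + 2r members and the no-access group has s.

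- Expected proportion, toolset group: (0.10s + 2rq)/(s + 2r); no-access group: 0.10.
- Rejection probability: Φ((d − 1.96·SE₀)/SE₁) + Φ((−d − 1.96·SE₀)/SE₁), where d is the expected difference, SE₀ the pooled and SE₁ the unpooled standard error.

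Example, r = 50 and q = 0.238: s = 550. The toolset proportion is (55 + 23.8)/650 = 12.1%, so d = 0.0212. SE₀ = 0.0182 and SE₁ = 0.0181. The first term is Φ(−0.80) = 0.21 and the second is about 0.001.

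| Referrals per arm (r) | Mix of referrals (q) | Group sizes | Expected African American | False-positive rate |
|---|---|---|---|---|
| 5 | 23.8% | 605 v 595 | 10.2% v 10% | 5% |
| 20 | 23.8% | 620 v 580 | 10.9% v 10% | 8% |
| 50 | 23.8% | 650 v 550 | 12.1% v 10% | 21% |
| 100 | 23.8% | 700 v 500 | 13.9% v 10% | 54% |
| 50 | 15% | 650 v 550 | 10.8% v 10% | 7% |
| any | 10% | – | 10% v 10% | 5% |

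**Simulation check** (100,000 trials per scenario, q = 23.8%). False positives are 27% when 10% of the 1200 are peer-recruited (60 per arm) and 66% when 20% are. At 30% the spurious difference is 6.4 points, larger than the smallest difference the trial was sized for (6 points). With each recruit counted in the recruiter's randomised arm, the rate is 4.6% to 5.0% throughout. All these rates treat participants as independent; clustering within chains would change them.

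**With a real toolset effect** (475 direct recruits per arm, 200 peers from toolset holders, 50 from controls, q = 23.8%):

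- By origin: (47.5 + 47.6)/675 = 14.1% v (47.5 + 11.9)/525 = 11.3%, a difference of 2.8 points.
- By the access rule: (47.5 + 59.5)/725 = 14.8% v 10%, a difference of 4.8 points.
- With only 10 control referrals (495 direct recruits per arm), the differences are 3.7 and 4.1 points.

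**The case against.** The strongest reply is that H1A, as worded in the hypotheses box, compares recruitment methods. On that reading a word-of-mouth recruit belongs on the peer side and nothing is misclassified. This stands as a reading, and parts of the sample size and analysis text speak of recruitment methods. But a comparison by source is not randomised, and it does not answer the question about access that the toolset section poses.

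A second reply is that the rule governs who receives the toolset and that analysis grouping may be set out in a fuller document. That is fair as far as it goes. However, this article defines the comparator by lack of access, so on its own terms recruits with access cannot be in it.

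Third, referral by the no-toolset arm is nowhere described. The Recruitment section mentions recruiting only for participants who hold the toolset. This stands, and it limits the size of the concern. A reader might infer from the Table 1 item "Use of tools outside the Smoker-2-Smoker peer recruitment toolset" that the plan expects control participants to recruit. The item sits among questions about a recruiter's experience and may concern only toolset holders using other channels, so it does not show this.

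A reader might also infer that the count of peers recruited is biased in the same way. The protocol states no between-arm test of those counts, so there is no planned analysis for the bias to affect.

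**Conclusion.** The point holds conditionally. If H1A tests the effect of toolset access, the planned grouping is not protected by randomisation and can produce a difference when there is no effect. That much follows from the access rule, the comparator's definition and the unadjusted chi-square.

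The size is not known. It depends on how many peers no-toolset participants bring in and on their racial mix, and the protocol gives neither. The 23.8% is borrowed from pilot peer recruits in a study where smokers had peer-recruitment access; unaided word of mouth may differ. Over the range examined, the false-positive rate runs from the nominal 5% (few referrals, or referrals with the same mix as direct recruits) to 54% (100 per arm at 23.8%). A reader might take the upper figures as a forecast that H1A will be falsely positive; they only illustrate what the rule permits.

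This should be fixed, but it does not undermine the trial as a whole. The Abstract names cessation and risk reduction as primary, although the sample size section calls H1A's comparison the primary aim. The effectiveness randomisation is unaffected.

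**What to change.** 1. State that H1A's primary contrast is by randomised toolset access.
2. Leave the access rule as it is. For H1A, assign each recruit to the randomised toolset arm of the directly recruited smoker at the head of the chain, using the recruiter marker described in Statistical Analyses. Recruits traced to a no-toolset smoker count in the no-toolset arm.
3. Replace the plain chi-square with a comparison of proportions whose standard errors allow for clustering by chain. A direct recruit who recruits nobody is a chain of one.
4. Report recruits with no traceable recruiter separately, with a sensitivity analysis that places them all in one arm and then all in the other.
5. Label any comparison of peer-recruited with online-recruited smokers as non-randomised.

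The cost is one derived grouping variable and a changed H1A test. The expected difference becomes smaller wherever control participants do recruit (2.8 instead of 4.8 points in the example), clustering will usually widen the interval, and some recruits will be untraceable. A new registration question about the recruiter would no longer help, because the Abstract reports enrolment complete. The regrouping therefore depends on what the recruiter marker already holds.

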### Study Design

As noted in Figure 1, all participants registering online on the Decide2Quit DISC will first undergo an effectiveness randomization and then a peer recruitment allocation. The effectiveness randomization will randomly assign participants to either receive access to the recommender system CTHC or the standard CTHC. The peer recruitment allocation will depend on the recruitment source. As noted in the section below, we will either directly recruit participants to the study (via search engine advertisements and research match) or they will be recruited by their peers (peer recruited). Directly recruited peers will be randomized to either receive the peer recruitment toolset or not receive the toolset. All peer recruited participants will receive access to the peer recruitment toolset. We are using this approach for the peer recruited smokers to enhance blinding. This decision was made because these recruited smokers may communicate with their peers about the intervention.

### Recruitment

#### Process

Our primary recruitment method will be to directly recruit smokers online using search engine advertisements or ResearchMatch. Participants having access to the peer recruitment toolset will be able to recruit their friends and family smokers to the website. To recruit via search engine advertisements, we will develop and post online advertisements customized to appear to smokers searching for quit smoking–related search terms online. When smokers click on these advertisements, they are redirected to Decide2Quit, where they are provided study information and registration instructions. The functions are provided in the ad managers of the search and social media website-targeted ads for smokers. For example, the Facebook ad manager allows advertisers to target users based on their interests derived from their profile’s keywords, pages they like, and groups they visit, which are then displayed on the Facebook page of the user. ResearchMatch is a free and secure online tool developed by Vanderbilt University and used by academic institutions across the country. To register, volunteers enroll on the ResearchMatch website, fill out demographic and optional health history questionnaires, and submit their profile. As noted, we will test peer recruitment for increasing access to the Decide2Quit DISC. Thus, we may also have participants who are peer recruited to the study as a consequence of our peer recruitment experiment.

